## Abstract

**Background:**

Up to 30% of patients suffer from long-term functional restrictions following conservative treatment of distal radius fractures. Whether duration of cast immobilisation influences functional outcome remains unclear.

**Methods/Design:**

The aim of the study is to evaluate whether the duration of immobilization of non or minimally displaced distal radial fractures can be safely reduced. We will compare three weeks of plaster cast immobilization with five weeks of plaster cast immobilization in adult patient with non or minimally displaced distal radial fractures.

Study design: a prospective randomized clinical trial.

Study population: adult (>18 years) (independent in activities of daily living) patients with a non/minimal displaced distal radius fracture (dorsal angulation <15°, volar tilt <20°, radial inclination >15°, ulnar positive variance <5 mm and an articular step off <2 mm).

Intervention: three weeks of plaster cast immobilization versus five weeks of plaster cast immobilization.

Main study parameters: primary outcome parameters: Patient related wrist evaluation (PRWE) Quick Disability of Arm, Shoulder and Hand (QUICKDASH) score after a one year follow-up, and secondary parameters: range of motion, pain level (VAS) and complications.

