**Discussion:**

The expectation of this study is that shorter duration of plaster cast immobilisation is beneficial for the patient with a distal radius fracture. This risk of specific complications is low and generally similar in both treatment options. Moreover, the burden of the study is not much higher compared to standard treatment. Follow-up is standardized according to current trauma guidelines. Literature indicates that both treatment options from the study are accepted for displaced distal radius fractures. No clear advantage for one treatment options is found at present in the literature, although there is no level I evidence present. This trial will provide level-1 evidence for the comparison of consolidation and functional outcome between two treatment options for non-displaced distal radial fractures. The gathered data may support the development of a clinical guideline for conservative treatment of distal radial fractures.

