## Background

Fractures of the distal radius are common injuries and account for up to 15% of all extremity fractures [1]. Most of these patients can be treated non-operatively in a plaster of Paris, with excellent functional results [2,3]. Usually a immobilization period of four till six weeks is preferred. The duration of immobilisation has been questioned earlier in literature. Some authors believe that three weeks is long enough [4-6], while others consider one week of immobilization is sufficient [7]. Other authors even consider that there is no need for plaster immobilsation in case of a non-displaced distal radial fracture [8,9].

The duration of immobilization of distal radius fractures depends on whether these fractures can displace into an unacceptable position. Most radial fractures are liable to displace within the first two weeks [10], only 7% to 8% displace after this time [10,11], and none after six weeks [12]. A minimum period of three weeks of immobilization seems safe.

Two randomized controlled trials compared three-weeks with five-weeks immobilization in a plaster back slab, in a total of 133 patients [5,6]. Most patients had minimally displaced distal radial fractures. Both trials found no significant differences in either anatomical or functional outcomes after 9 months [5] and one year [6] follow up. Separate data for complications were not given. Jensen’s RCT in 1997 showed in 62 patients with an undisplaced extra-articular distal radius fracture that even one week of immobilization did not differ from three weeks of immobilization when comparing radiographic results or functional outcome defined by the, Gartland and Werley score after 26 weeks [7]. Separate results for complications were not provided.

The studies mentioned above have their limitations in follow-up, modest patient groups or methods. In a review of Handoll 2008 concerning conservative interventions for treating distal radial fractures in adults it was also concluded that there is no scientific support for a preferred treatment strategy, including length of immobilization, for non-displaced distal radial fractures [13].

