### Sample size

The primary outcome will be the QuickDASH score of which the minimal clinically important difference is 14 points. Based on a difference of 14 points, the sample size of 30 patients per treatment group was calculated with a power (1-β) of 80 percent and a type I error (α) of 5 percent, allowing for 10 percent drop-out. In total 70 patients will be included.

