#### *Univariate analysis*

The analysis of this study will be carried out according to the intention-to-treat principle, i.e. the patients will remain in the group they will be randomly allocated to at baseline. Analysis of functional outcome will be assessed using repeated-measures analysis of variance (GLM 4) with the time as the within-group factor and the treatment as the between-group factor. Post-hoc analysis will be performed on the time of randomization. Group comparisons at the different time points will be made only when the overall repeated-measures tests are statistically significant. All scores will be tested for normality using the Kolmogorov-Smirnov test. Parametric variables will be compared using the Student’s t-test, while non-parametric and ordinal variables will be compared using the Mann–Whitney U statistic. Nominal variables will be compared across independent groups using the chi-squared test or Fisher’s exact test. Homogeneity of variance will be assessed using Levene’s test. Also a multiple regression will be performed. SPSS statistical software (version 11.0.1) will be used for the analysis, in which two-tailed P value < 0.05 will be considered significant.

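### The protocol asks both whether a shorter cast is safe and whether it is better; the planned gated difference test serves only the second question

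*Protocol article*

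**What the plan says.** **The question.** The Methods/Design part of the abstract gives the aim as to "evaluate whether the duration of immobilization of non or minimally displaced distal radial fractures can be safely reduced". The discussion part of the abstract says: "The expectation of this study is that shorter duration of plaster cast immobilisation is beneficial". The Background suggests that a short period could hasten recovery, and the closing Discussion asks whether shorter periods are favorable. The Rationale section speaks neutrally of comparing results.

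**The sample size.** This section takes QuickDASH as primary and puts its smallest clinically important difference at 14 points. The number per group follows from that figure: "Based on a difference of 14 points, the sample size of 30 patients per treatment group was calculated". Power is set at 80% and two-sided alpha at 5%, and the total comes to 70 once a 10% drop-out is allowed for. No SD is given.

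**The analysis.** The Univariate analysis section plans a repeated-measures analysis of variance and a threshold at which a "two-tailed P value < 0.05 will be considered significant". It allows group comparisons at individual time points only if the overall repeated-measures tests are significant. The abstract names the scores after one year of follow-up as primary.

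**Earlier evidence.** On two earlier randomized trials of three against five weeks (133 patients in all), the Background reports: "Both trials found no significant differences in either anatomical or functional outcomes after 9 months". For the second trial the follow-up was one year.

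**The concern.** To say that immobilization can be safely reduced is to say that three weeks is not importantly worse than five. A non-significant test of difference does not establish that, because the data may still allow an important disadvantage. The protocol gives 14 points only as a difference to detect. It does not use it as a limit that the confidence interval must exclude.

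The significance gate adds to the problem. After a null overall test, the plan omits the one-year between-group comparison, which is the estimate that the safety question needs. Because both earlier trials of this comparison found no significant difference, a null result is a realistic prospect. The aim in the abstract would then have no pre-stated answer, although the abstract hopes that the data may inform a guideline.

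**Working it through.** **Inputs.** From the Sample size section: difference 14 points, 30 per group, power 80%, two-sided alpha 5%, drop-out 10%. The SD is not stated and has to be assumed.

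**Reproducing the plan's figure.** The 30 per group cannot be reproduced independently without an SD; one can only ask which SD it implies.
- Normal approximation: SD = 14 / [(1.96 + 0.84) × √(2/30)] = about 19.35.
- Two-sample t-test with 58 degrees of freedom: SD = 19.03, used below.
- If only 27 per group were evaluable, the normal approximation gives about 18.4.
- Drop-out: 30/0.90 = 33.3, so 34 per group or 68 in total, close to the stated 70.

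**Precision of the comparison**, 30 evaluable per group:
- SE = 19.03 × √(2/30) = 4.91.
- Half-width of the 95% CI = 2.00 × 4.91 = 9.84.
- Let d be the observed difference, three minus five weeks; positive means three weeks is worse. The result is non-significant if |d| < 9.84. The upper limit exceeds 14 if d > 14 − 9.84 = 4.16.
- So any d between 4.16 and 9.84 is non-significant and still compatible with 14 points of harm. A just non-significant result has an upper limit of about 2 × 9.84 = 19.7.

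**How often, if three weeks is truly 7 points worse** (7 is chosen for illustration, half of 14):
- Non-significant: Φ((9.84 − 7)/4.91) − Φ((−9.84 − 7)/4.91) = 0.72.
- Non-significant with 14 not excluded: Φ((9.84 − 7)/4.91) − Φ((4.16 − 7)/4.91) = 0.718 − 0.282 = 0.44.

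**How often the upper limit lies below 14 at a true difference of zero:** Φ((14 − 9.84)/4.91) = 0.80. For a 10-point limit: Φ((10 − 9.84)/4.91) = 0.51.

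**Range over assumed SDs**, same formulas:

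| Assumed SD | SE | Half-width | Non-significant, 14 not excluded | Chance of this if truth is 7 | Chance upper limit < 14 if truth is 0 |
|---|---|---|---|---|---|
| 15 | 3.87 | 7.75 | 6.25 to 7.75 | 15% | 95% |
| 19.03 | 4.91 | 9.84 | 4.16 to 9.84 | 44% | 80% |
| 25 | 6.45 | 12.92 | 1.08 to 12.92 | 64% | 57% |

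The 80% in the middle row is not independent support for the sample size. The SD was solved from 80% power at 14 points, so the same figure has to come back.

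**The case against.** **This is a superiority trial.** The stated expectation is benefit, the Background and the closing Discussion point the same way, and the aim says only that the trial will evaluate whether a reduction is safe. A two-sided test sized on the minimal clinically important difference suits that hypothesis. This stands. A reader might infer that the design cannot answer the trial's question at all; the documents do not support that, because it serves one of two stated questions. It leaves the other unserved.

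**No misreading is written down.** A reader might infer that the protocol would take p > 0.05 as proof of safety and carry it into a guideline. It contains no such rule, and says only that the data may support guideline development. The Descriptive statistics section also promises 95% confidence intervals. Those are for mean scores, however, and no interval for the between-group difference is explicitly promised.

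**The SD is not in the protocol.** This is correct, and the 44% depends heavily on it. With the SE treated as known, the band of results in question vanishes once the half-width falls below 7, that is, for an SD below about 7/(2.00 × 0.258) = 13.5.

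**Safety on complications.** It is tempting to add that the trial lacks power for complications, using the 7% to 8% late displacement in the Background. That figure is not specific to the fractures enrolled, counts the third week when both groups are still in plaster, and is not a rate for either arm. Complications are secondary and the trial was not sized on them, so low power there is not an error.

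**Detail belongs in the SAP.** Adherence-based sensitivity analyses and exact intervals for complications may well be there, and their absence is not faulted. The hypothesis, the role of the 14 points and the significance gate are fixed in this document.

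**Conclusion.** The point holds as a mismatch between two stated questions and a test that serves one of them, made worse by a gate that would suppress the one-year comparison after a null overall test. This takes the gate to refer to the tests involving treatment; the protocol does not say which overall test opens it.

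The size depends on the SD. With about 19 assumed and 30 evaluable per group, an observed disadvantage of roughly 4.2 to 9.8 points would be non-significant and leave 14 points open. At a true disadvantage of 7 points that would occur in about 44% of trials, with a range of 15% to 64% for SDs of 15 to 25.

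A reader might infer that the trial is too small for the safety question on QuickDASH. The figures do not show that: at a true difference of zero and the implied SD, an ordinary 95% CI would exclude 14 points about 80% of the time. What is missing is a stated hypothesis and a reading of the interval that is not gated. That a null result is plausible is an inference from the two earlier trials. The matter should be corrected, but it does not invalidate the design.

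**What to change.** 1. State which hypothesis is primary, and align the aim, the expectation and the sample size section with it.
2. Always estimate the 12-month QuickDASH difference, three minus five weeks, with its 95% CI, whatever the overall repeated-measures test shows.
3. Conclude that three weeks is not importantly worse only if the upper limit lies below a limit justified in advance and no larger than the protocol's own 14 points. Otherwise call a non-significant result inconclusive. Using the full 14 points as the limit is lenient and needs its own justification.
4. If the limit is met, test superiority on the same interval; no alpha split is needed. If PRWE stays primary, it needs a limit of its own.
5. State the SD behind the 30 per group.
6. Say in the conclusions that the trial cannot by itself establish safety on complications.

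The cost is wording, plus two consequences to accept. Some null results must be reported as inconclusive. Power to meet the limit also depends on the unstated SD: at 14 points and a true difference of zero it is about 95%, 80% and 57% for SDs of 15, 19 and 25, and for a 10-point limit about 51% at an SD of 19. A limit tighter than 14 points may therefore require more patients.

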**Discussion:**

The expectation of this study is that shorter duration of plaster cast immobilisation is beneficial for the patient with a distal radius fracture. This risk of specific complications is low and generally similar in both treatment options. Moreover, the burden of the study is not much higher compared to standard treatment. Follow-up is standardized according to current trauma guidelines. Literature indicates that both treatment options from the study are accepted for displaced distal radius fractures. No clear advantage for one treatment options is found at present in the literature, although there is no level I evidence present. This trial will provide level-1 evidence for the comparison of consolidation and functional outcome between two treatment options for non-displaced distal radial fractures. The gathered data may support the development of a clinical guideline for conservative treatment of distal radial fractures.

**Trial registration:**

Netherlands National Trial Register NTR3552.

## Background

Fractures of the distal radius are common injuries and account for up to 15% of all extremity fractures [1]. Most of these patients can be treated non-operatively in a plaster of Paris, with excellent functional results [2,3]. Usually a immobilization period of four till six weeks is preferred. The duration of immobilisation has been questioned earlier in literature. Some authors believe that three weeks is long enough [4-6], while others consider one week of immobilization is sufficient [7]. Other authors even consider that there is no need for plaster immobilsation in case of a non-displaced distal radial fracture [8,9].

The duration of immobilization of distal radius fractures depends on whether these fractures can displace into an unacceptable position. Most radial fractures are liable to displace within the first two weeks [10], only 7% to 8% displace after this time [10,11], and none after six weeks [12]. A minimum period of three weeks of immobilization seems safe.

Two randomized controlled trials compared three-weeks with five-weeks immobilization in a plaster back slab, in a total of 133 patients [5,6]. Most patients had minimally displaced distal radial fractures. Both trials found no significant differences in either anatomical or functional outcomes after 9 months [5] and one year [6] follow up. Separate data for complications were not given. Jensen’s RCT in 1997 showed in 62 patients with an undisplaced extra-articular distal radius fracture that even one week of immobilization did not differ from three weeks of immobilization when comparing radiographic results or functional outcome defined by the, Gartland and Werley score after 26 weeks [7]. Separate results for complications were not provided.

The studies mentioned above have their limitations in follow-up, modest patient groups or methods. In a review of Handoll 2008 concerning conservative interventions for treating distal radial fractures in adults it was also concluded that there is no scientific support for a preferred treatment strategy, including length of immobilization, for non-displaced distal radial fractures [13].

For example the Gartland and Werley score [14] was used to assess functional outcome in two studies [5,7]. This is the most commonly described instrument in the literature for evaluating outcome after wrist surgery, but it has not been validated so to date. In the other study radiography, wrist motion, grip strength and pain were measured after one year and no outcome measure instruments were used [6]. Thereby in all the studies serious complications were not reported separately, patient satisfaction and resource implications were rarely mentioned and there was an inadequate description of inclusion criteria. The variety of fracture classification systems, with associated issues of reliability and validity further complicates comparison between studies and their outcomes [15].

Obviously, the ultimate treatment is short, safe and leads to an early return of function. In achieving this, reduction of the immobilization period may be beneficial. The short period of immobilization could speed up the functional recovery or reduce the number of days absent from work. Since there is little knowledge about the best immobilisation period for non-displaced distal radial fractures, there is a need for a RCT. In this study functional outcome will be the primary outcome and this will be assessed using validated instruments, namely the Patient Rated Wrist Evaluation (PRWE) and the Disability of Arm and Shoulder (DASH) forms [16].

### Rationale for the trial

Nowadays, usually an immobilization period of four till six weeks is preferred. Despite the minimal evidence in literature this immobilization period can be questioned. A randomized clinical trial with sufficient power is needed to provide scientific support for a preferred treatment strategy for non-displaced distal radial fractures. The aim of this trial is to compare the results of three weeks of cast immobilization with five weeks of cast immobilization of non-displaced distal radial fractures with respect to functional outcome, the incidence of non-union, pain scores, and complications.

## Methods/Design

### Study design

This study will be conducted as a prospective randomized clinical trial (see Figures 1 and 2) in which three weeks of plaster cast immobilization is compared with five weeks of plaster cast immobilization. Patients will be treated in a short arm plaster cast. Patients will only receive physiotherapy if necessary. The study started, September 1^st^, 2012.

**Figure 1 F1:**
[figure not shown]
Randomization and inclusion period.

**Figure 2 F2:**
[figure not shown]
Follow-up.

### Recruitment and consent

Patients with distal radius fractures will be initially managed on the emergency department. Using the criteria for displacement: distal radial fractures with initial dorsal angulation up to 15° and axial radial shortening of not more than 5 mm. Patients will be included if closed reduction of the distal radius fracture is not necessary according to these criteria for misalignment.

They will receive written information and a consent form from the attending physician, the clinical investigator or a research assistant. After providing informed consent, eligible patients will be randomized within one week. An independent research assistant will perform concealed permuted block randomization using a computer-generated randomization schedule after stratification for fracture type, gender and age. Allocation will be at random to four blocks.

### Blinding

#### *Functional status*

An independent research assistant will perform a blinded evaluation of the trial patients’ functional status.

#### *Radiographic outcome*

Radiographic evaluation of the alignment of the distal radius will be performed blinded for the intervention group. In addition to the treating physician, two independent experts will assess the Lidström score for the repeated X-rays of the wrist blinded from the first assessment (Figure 3).

**Figure 3 F3:**
[figure not shown]
Anatomical radiological classification for distal radial fractures according to Lidström.

### Bias prevention

To prevent bias stratification by age (younger and older than 60 years) and gender will be performed (Table 1).

**Table 1 T1:** Stratification by gender and age (younger and older than 60 years)

	**Patient characteristics**		**Randomization**
List 1	Male	Median age -	ABAB AABB ABBA BABA BAAB
List 2	Male	Median age +	BAAB BBAA ABAB AABB ABBA
List 3	Female	Median age -	AABB ABBA BAAB BBAA BABA
List 4	Female	Median age +	ABBA BABA ABAB AABB AABB

A = 3 weeks, B = 5 weeks.

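### Table 1 prints ordered allocation lists, their treatment key and a fixed block of four, which contradicts the stated concealment; whether these are the live lists must be clarified

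*Protocol article*

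**What the plan says.** All references are to the protocol article.

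- **Recruitment and consent (Methods/Design):** "An independent research assistant will perform concealed permuted block randomization using a computer-generated randomization schedule". The strata named there are fracture type, gender and age. Randomisation follows consent and takes place within a week. The section adds "Allocation will be at random to four blocks", which could mean four blocks or blocks of four. Information and consent forms may come from the attending physician, the clinical investigator or a research assistant.
- **Bias prevention, Table 1:** under a column headed Randomization, four lists are printed in order:
  - List 1 (male, lower age): "ABAB AABB ABBA BABA BAAB"
  - List 2 (male, higher age): "BAAB BBAA ABAB AABB ABBA"
  - List 3 (female, lower age): "AABB ABBA BAAB BBAA BABA"
  - List 4 (female, higher age): "ABBA BABA ABAB AABB AABB"

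  The footnote decodes them: "A = 3 weeks, B = 5 weeks". The caption sets the age cut at 60 years, but the rows speak of median age. Fracture type does not appear.
- **Study design:** "The study started, September" 2012, so the lists were printed for a trial already running.
- **Study population:** eligibility is evaluated at one named hospital, in the emergency or the outpatient department.
- **Blinding and Study procedures:** functional status, radiographs and range of motion are assessed blind. Nothing states that patients or treating staff are blinded to cast duration.
- **Sample size:** 70 patients in total.

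**The concern.** Concealment means that whoever decides on eligibility and obtains consent cannot know the next assignment. A printed sequence with its key removes that protection for any reader who can also count enrolments in a stratum. An independent person running the randomisation does not restore it.

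Several features give foreknowledge room to act. Eligibility turns on measured angulation and shortening and on a judgement that reduction is not needed. Up to a week may pass between consent and randomisation, so the order of entry could shift. Past assignments are visible, because patients and treating staff know who has a three-week and who a five-week cast.

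If recruiters favour one arm for certain patients, the groups differ from the start. Neither intention-to-treat analysis nor blinded assessment removes that difference. The primary outcomes, QuickDASH and PRWE, are self-reported by patients who know their treatment, so the blinded assessments do not cover them and a fair allocation is the main safeguard.

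**Working it through.** **Inputs.** The four lists and the key (Table 1); 70 planned patients (Sample size).

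**1. Structure of the lists.** Each list has 5 groups of 4 letters: 4 × 5 × 4 = 80 slots. Each of the 20 groups holds two A and two B. The printed block size is therefore fixed at four.

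**2. If the printed lists are live.** A reader with Table 1 and the count in a stratum knows every slot on that list. The number of patients covered is the sum over strata of min(n, 20), where n is the stratum's enrolment. The spread of the 70 is not given, so the range is:
- no stratum above 20 (for example 18 + 18 + 17 + 17 = 70): all 70 covered;
- an assumed uneven spread of 40 + 10 + 10 + 10: 20 + 10 + 10 + 10 = 50 of 70, or 71%;
- the extreme of all 70 in one stratum: 20 of 70, or 29%.

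The comparison of 80 slots with 70 patients therefore does not by itself show that every patient is covered.

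**3. If the printed lists are not live but the real schedule also uses fixed blocks of four.** Suppose someone knows the block size and the earlier assignments in the stratum.
- The fourth place in a block is always certain. The third is certain when the first two are equal.
- In theory, 2 of the 6 possible blocks start with two equal letters, so the certain share is (1 + 2/6) / 4 = 1/3.
- In the printed lists, blocks starting AA or BB number 1, 2, 2 and 2 in Lists 1 to 4, giving 7. Certain slots: 20 fourth places + 7 third places = 27 of 80, or 33.8%.

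**4. Best guess under the same knowledge.** The guesser always names the arm with more places left in the block and tosses a coin when they are equal.
- A block starting with two equal letters gives 0.5 + 0 + 1 + 1 = 2.5 expected correct guesses out of 4. Any other block gives 0.5 + 1 + 0.5 + 1 = 3.
- Printed lists: 7 × 2.5 + 13 × 3 = 56.5 of 80, or 70.6%.
- Theory: (2/6 × 2.5 + 4/6 × 3) / 4 = 70.8%, against 50% under simple randomisation.

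**5. Do the lists match the described schedule?** Recruitment and consent names three stratification factors; Table 1 uses two. Crossing gender and age with at least two fracture types would need at least 2 × 2 × 2 = 8 lists, and 4 are printed. The caption's 60-year cut and the rows' median age agree only if the median happens to be 60. On its face, then, Table 1 is not the complete schedule described elsewhere in the article.

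**The case against.** The strongest reply is that Table 1 may not be the working schedule. It lacks the fracture-type stratum, its age labels disagree, and its caption describes stratification. It could be an illustration or an earlier scheme. An independent assistant randomises, and does so after consent. Nothing shows that recruiting staff had the table or when they could have seen it.

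This reply stands against a stronger reading that a reader might infer: that the true sequence has been published and allocation was in fact not concealed. The document supports only the conditional statement. Four further limits also stand:

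- Full predictability is a ceiling. It needs the live list and an exact running count. The one-third figure needs the block size and all earlier assignments in the current block of that stratum. With two departments and at least four strata, tracking takes effort.
- The article places eligibility evaluation at one hospital but does not say where randomisation is done.
- Calling the trial unblinded would be too broad. Treatment is open to patients and treating staff, while three kinds of assessment are blinded.
- Repeating the primary analysis without every patient allocated under the disclosed lists might leave almost nobody, so it is not a sound general remedy.

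What the reply does not answer is the printed contradiction. The lists are ordered, decoded and unmarked as an example, in the article that asserts concealment. A condensed article may leave out details, but this problem lies in what it prints.

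**Conclusion.** The point holds in conditional form. Table 1 is incompatible with concealed allocation if its lists are operative: every printed assignment can then be foreseen, for somewhere between 20 and all 70 patients. If they are not operative, about one third of assignments remain certain in advance, and the best guess succeeds about 71% of the time. That second case assumes that the real schedule keeps fixed blocks of four and that earlier assignments are known.

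Selection bias at entry is possible under either condition. The document does not show that anyone used the lists, and the size or direction of any bias cannot be derived from it. The mismatches in strata and age labels leave real doubt about the lists' status, and only the investigators can settle it.

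**What to change.** 1. State whether the lists in Table 1 are or were the live schedule, and who had access to them and from when. Reconcile them with the fracture-type stratum, and settle whether the age cut is 60 years or the median.
2. For patients not yet randomised, generate new lists with randomly varying block sizes that are not disclosed to recruiting staff. Someone outside recruitment should release assignments one at a time, after consent and entry of the stratum. This step applies only if recruitment is still open, which the article does not say.
3. Replace Table 1 with a description of the method: strata, type of randomisation, who holds the list and how it is released. Print no sequence and no block size while recruitment continues.
4. In the final report, give the number of patients randomised under disclosed lists. Compare baseline characteristics and results before and after the change only if enough patients were randomised after it.

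The cost is a few hours for new lists plus a protocol note. The statistical downside is small: the largest possible imbalance within a stratum is half the largest block, so it rises slightly above the 2 patients allowed by blocks of four.
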